### Data integrity and monitoring

An independent Data Safety Monitoring Committee (DSC) (an independent researcher not a member in the coauthor’s group) will be assembled and responsible for assessing trial safety and ensuring that the best interests of participants are observed at all times. A single data quality audit will be performed during the study period, once 50% of the sample size is reached.

Furthermore, data will be stored in password-protected spreadsheets on secured servers hosted by the University of Sydney, which will be regularly scrutinised for omissions and errors, and then transferred to appropriate statistical software for analysis by an investigator blinded to group allocation. All the data collected will be restricted to the lead investigator and selected members of the research team using the backend of the project. A REDCap code will be created to allow re-identification when necessary.

### Sample size

Sample size calculation was based on the between-group difference of 3 points on our primary outcome, i.e. PSFS (0–30 points)) which has been reported as the scale’s minimum clinically important difference (MCID) for both Knee OA and LBP [53, 54]. In our previous study of physical activity and exercises for LBP, the response within each subject group on physical function was normally distributed with a standard deviation of 7 [54]. A sample size of 78 per group (total of 156 participants) will achieve 80% power (Type I error of 0.05) to detect an MCID of 3 points on physical function [55] (adjusted for scale score range of 0–30), allowing for a loss to follow-up rate of 15% at six months. Calculations were performed with Stata IC/13.0 power two means function.

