## Methods

### Aim

The primary aim of this study is to investigate the effectiveness of a three-month physiotherapist-delivered eHealth intervention comprised of a tailored physical activity plan and progressive resistance exercise program, to improve physical function in people living in rural Australia with chronic non-specific LBP or knee OA, compared to usual care.

The secondary aim is to evaluate the effectiveness of the intervention to improve pain intensity, activity limitations, quality of life, physical activity levels, and pain coping compared to usual care. We will also collect process evaluation data such as recruitment rate, attendance and adherence, follow-up rate, participants’ opinions and any difficulties or barriers encountered throughout the trial. We hypothesise that the eHealth intervention will be effective and will result in better levels of physical function compared to usual care.

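### The sample-size section claims 80% power with 78 per group but does not state sidedness: power is about 69% for a two-sided 5% test, and only an undeclared one-sided test comes close to 80%

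*Protocol article*

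**What the plan says.** The protocol article's Sample size section sets out one calculation for the primary outcome. The target effect is fixed by "Sample size calculation was based on the between-group difference of 3 points on our primary outcome". The variability comes from a previous study by the same group, where "the response within each subject group on physical function was normally distributed with a standard deviation of 7". The result is "A sample size of 78 per group (total of 156 participants) will achieve 80% power (Type I error of 0.05"), "allowing for a loss to follow-up rate of 15% at six months". The method is named: "Calculations were performed with Stata IC/13.0 power two means function".

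The error rate is given only as "Type I error of 0.05". Neither this section nor the Statistical analysis section says whether the test has one or two sides. The Aim section words the hypothesis directionally: "We hypothesise that the eHealth intervention will be effective and will result in better levels of physical function compared to usual care". The Statistical analysis section plans linear mixed models with the baseline value as covariate, but no baseline–outcome correlation or repeated-measures gain enters the printed calculation.

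**The concern.** A bare 5% type I error in a superiority comparison is normally read as two-sided. On that reading the printed inputs do not lead to 80% power at 78 per group, and the gap is too large for rounding. Power would fall short even if nobody were lost to follow-up.

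This is the trial's only sample-size justification, and it concerns the primary outcome. If the test is two-sided and unadjusted, the chance of missing a true 3-point effect is about 31% rather than 20%. A reader who trusts the printed 80% would then take an inconclusive result as firmer evidence against a 3-point benefit than it is.

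**Working it through.** **Inputs (all from Sample size)**
- Difference 3 points; SD 7; standardised difference 3/7 = 0.429.
- Type I error 0.05, sidedness not stated; power 80%.
- 78 per group, 1:1; 15% loss, so 78 × 0.85 = 66.3, taken as 66 analysed per group.
- Two-sample comparison of means, with no correlation.

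**Step 1. Reproduce the plan's 78.** The normal formula for n per group is 2 × (z_α + z_β)² × SD² / difference².
- One-sided 5%: 2 × (1.645 + 0.842)² × 49 / 9 = 67.3, so 68 analysed per group. Then 68 × 1.15 = 78.2, which rounds to 78.
- Inflating for 15% loss calls for division by 0.85: 68 / 0.85 = 80.
- Two-sided 5%: 2 × (1.960 + 0.842)² × 49 / 9 = 85.5, so 86 analysed per group. Then 86 / 0.85 = 101.2, so 102; even 86 × 1.15 = 98.9, so 99. Neither is near 78.

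Of these routes, only the one-sided one comes close to the printed figure.

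**Step 2. Power at the planned size.** This uses the noncentral t distribution with 2n − 2 degrees of freedom and noncentrality 3 / (7 × √(2/n)). At n = 66 the standard error is 7 × √(2/66) = 1.219 and the noncentrality is 3 / 1.219 = 2.46.

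| Analysed per group | Two-sided 5% | One-sided 5% |
|---|---|---|
| 66 (after 15% loss) | 68.6% | 78.9% |
| 78 (no loss) | 75.8% | 84.6% |

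The normal approximation gives 69.2% and 79.3% at 66 per group, so the choice of formula does not matter.

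**Step 3. What two-sided 80% would need.**
- By the t calculation, 87 analysed per group; 87 / 0.85 = 102.4, so 103 enrolled per group (206 in total).
- With 66 analysed per group, the difference detectable with 80% power is 3.44 points rather than 3.

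**Step 4. Could the planned baseline adjustment supply the missing power?** The documents give no correlation, so rho below is an assumption. The answer also depends on what the SD of 7 describes.
- If it is the SD of follow-up scores, the adjusted SD is 7 × √(1 − rho²).
- If it is the SD of change scores, and variances are equal at baseline and follow-up, the adjusted SD is 7 × √((1 + rho)/2).

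Two-sided power at 66 per group:

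| Assumed rho | SD 7 = follow-up scores | SD 7 = change scores |
|---|---|---|
| 0.3 | 72.6% | 85.8% |
| 0.4 | 76.0% | 83.2% |
| 0.5 | 80.6% | 80.6% |
| 0.6 | 86.3% | 78.0% |

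On the first reading 80% needs rho of at least about 0.49; on the second it needs rho of at most about 0.52. The condition reverses, and the section's wording (the response within each group) does not settle which applies.

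**The case against.** The strongest counter-argument is that the document never says the test is two-sided. A one-sided 5% test brings the printed figure within about one point of 80%, and the directional hypothesis in the Aim section is compatible with it. This stands in part. A reader might infer that 80% power simply cannot follow from the stated inputs, or that power is overstated by 11 points whatever the test. The document does not support either statement: sidedness is a missing input, and one choice of it nearly reproduces the claim. But a directional hypothesis states an expected result; it does not declare a one-sided test. A one-sided 5% test is a material choice that has to be stated.

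A second argument is that the planned analysis adjusts for baseline and puts estimates ahead of significance tests, so 69% is not the power of the analysis that will be run, and readers will look mainly at the interval. This also stands in part. It softens the consequence, and it means that 69% must be labelled as the unadjusted figure. It does not rescue the printed statement, which names an unadjusted two-means calculation and assumes no correlation. Nor can one required correlation be read off as a condition for 80%, because its direction depends on the meaning of the SD.

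The inflation by 1.15 instead of division by 0.85 is an inferred route to 78, not one the document states. It accounts for only two participants per group.

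**Conclusion.** The point holds conditionally. As printed, 80% power with 78 per group is approximated only by an undeclared one-sided 5% test, with power of about 79% after 15% loss. Under the conventional two-sided 5% test, the same inputs give about 69% with 66 analysed per group and about 76% with no loss, and 80% would need about 103 enrolled per group, 25 more than planned.

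The 11-point shortfall and the 31% risk of missing a 3-point effect therefore apply to a two-sided, unadjusted comparison with SD 7 and 15% loss in each group. Whether the baseline-adjusted analysis reaches 80% cannot be determined from the document.

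**What to change.** Keep 156 participants and state the sidedness in the sample-size section. Then take the branch that applies:

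- **Two-sided, unadjusted:** restate the power as about 69% for 66 analysed per group, with a detectable difference of about 3.4 points at 80% power.
- **Two-sided, baseline-adjusted:** re-base the calculation on the analysis in the Statistical analysis section. Say whether the SD of 7 is a follow-up or a change-score SD, and show power over a range of assumed baseline–outcome correlations, such as 0.3 to 0.6, rather than a single threshold.
- **One-sided:** declare it, justify it, and state power of about 79%.

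The cost is a change of wording in the sample-size statement, carried into the registry entry and analysis plan where they repeat it. No participants are added and no endpoint or analysis changes. The downside is a less favourable stated power, unless a baseline-adjusted calculation can be justified.

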### Statistical analysis

Descriptive characteristics, as well as baseline outcome measures, will be used to assess baseline comparability between groups. Analyses will be by intention to treat and performed by a blinded statistician. No attempt will be made to impute missing values. The focus of the analyses will be on effect estimation rather than formal hypothesis testing. The following covariates will be accounted in the models if found to be different between groups: the effect of baseline pain and disability levels, symptom length, comorbidities, and age. The effect of group allocation on continuous outcomes (e.g. function, physical activity) will be assessed through group*time interaction terms using linear mixed models with baseline value as covariate (mixed command in Stata 15). A subgroup analysis stratified by condition (LBP or OA) will be performed separately. A statistical analysis plan will be made publicly available before analysis.

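### Covariates enter the models only if the groups look different at baseline; the set should instead be fixed in advance

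*Protocol article*

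**What the plan says.** All of this stands in the Statistical analysis section of the protocol article.

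- Baseline descriptives and baseline outcome measures "will be used to assess baseline comparability between groups".
- The selection rule follows: "The following covariates will be accounted in the models if found to be different between groups". The list is "the effect of baseline pain and disability levels, symptom length, comorbidities, and age", which gives five candidates.
- Continuous outcomes are analysed through group-by-time terms, "using linear mixed models with baseline value as covariate". This adjustment carries no condition.
- On purpose: "The focus of the analyses will be on effect estimation rather than formal hypothesis testing".
- On what is still to come: "A statistical analysis plan will be made publicly available before analysis".

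The section names no test, threshold or size of difference that would make a covariate count as different. Nothing elsewhere in the article overrides the rule.

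**The concern.** Allocation is random, so any baseline difference between the groups is a chance event. The reason to adjust for a covariate is that it predicts the outcome, and observed imbalance carries no information about that. The rule can therefore admit a useless variable that happens to be unbalanced and leave out a strongly prognostic one that happens to be balanced.

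Three things follow.

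1. The covariate subset behind the primary estimate is unknown until the baseline data are compared.
2. Precision that the listed variables could supply is given up in most realisations of the trial.
3. The standard error from the chosen model treats the subset as if it had been fixed. A covariate is left out only when its imbalance is small, yet the model then reports an error that allows for imbalance of any size. The reported error is therefore somewhat too large. This matters in a trial whose declared product is an estimate with its interval.

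There is also a small wording clash. For the pain and disability outcomes, the baseline measure is conditional under one sentence and always included under another.

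**Working it through.** **Inputs from the document.** The Sample size section gives a "between-group difference of 3 points on our primary outcome", outcomes "normally distributed with a standard deviation of 7", 78 per group, 80% power, Type I error 0.05 and 15% loss. Completers: 78 × 0.85 = 66.3, taken as 66 per group (N = 132).

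**The plan's own figure, for scale only.** No figure is attached to the covariate rule. For the 78 per group:
- one-sided: 2 × (7 × (1.645 + 0.842) / 3)² = 67.3, and 67.3 × 1.15 = 77.4, so 78;
- two-sided, unadjusted: 85.5, and 85.5 / 0.85 = 100.5;
- two-sided with baseline adjustment at r = 0.5: 65, which becomes 77 after allowing for loss.

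The article does not state sidedness. The sample size is not in dispute here.

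**Assumptions not in the document.** The correlation of baseline with follow-up outcome is 0.5. The five candidates are independent and together explain a share R² of the variance left after the baseline outcome, from 0 to 0.4. The trigger is p<0.05 or p<0.20. A single-time-point analysis of covariance stands in for the mixed model.

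**Step 1: how often the set changes.** Five candidates allow 2⁵ = 32 subsets. The chance that at least one is triggered is 1 − (1 − p)⁵:
- p<0.05: 1 − 0.95⁵ = 23%
- p<0.10: 41%
- p<0.20: 67%

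**Step 2: precision by formula.** With the baseline outcome only, SE = 7 × √(1 − 0.5²) × √(2/66) = 1.06. Adding five covariates in every trial multiplies this by √(1 − R²) and by a small penalty for chance imbalance, about √(128/123) = 1.02.
- R² = 0: 1.06 × 1.02 = 1.08
- R² = 0.3: 1.06 × 0.837 × 1.02 = 0.90

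The simulated mean reported SEs for fixed adjustment are 1.08 and 0.90, which agree.

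**Step 3: simulation.** 10,000 trials per setting, true difference 3, two-sided 0.05, trigger p<0.05:

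| R² | SD of estimate: rule / always | Power: rule / always | Reported SE ÷ true SD, rule | Type I error, rule |
|---|---|---|---|---|
| 0 | 1.05 / 1.07 | 80% / 79% | 1.01 | 0.046 |
| 0.1 | 1.06 / 1.03 | 80% / 83% | 1.01 | 0.051 |
| 0.2 | 1.03 / 0.97 | 81% / 87% | 1.03 | 0.042 |
| 0.3 | 1.03 / 0.91 | 81% / 91% | 1.03 | 0.042 |
| 0.4 | 1.01 / 0.83 | 82% / 95% | 1.05 | 0.042 |

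The Monte Carlo error of a 5% rate is √(0.05 × 0.95 / 10,000) = 0.002. The first two rows therefore cannot be told apart from nominal calibration at this number of trials. The lower three show a real but mild conservatism.

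**Step 4: a looser trigger.** At p<0.20 the rule recovers more precision (84% power against 91% at R² = 0.3), but its calibration is worse. For R² from 0.1 to 0.4 the SE ratio runs from 1.01 to 1.11 and the Type I error from 0.048 to 0.029. Fixed adjustment keeps a ratio of 0.99 to 1.01 and a Type I error of 0.048 to 0.053 throughout.

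**The case against.** **The model is mostly fixed.** The section fixes the model class, the group-by-time terms, the outcome's own baseline value and a closed list of candidates. A reader might infer that the whole primary model is undefined. It is not; only the subset of five is open. Selection looks at baseline data and not at outcomes, and the statistician is blinded, so there is little room to steer the result. This stands, but blinding does not make chance imbalance a sound criterion.

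**The SAP may supply the threshold.** It may, and the missing threshold is not held against the article. Any threshold would still select on imbalance, so the fault lies in the stated rule. Nor does the article say that baseline significance tests will be run; the p-value triggers above are assumptions.

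**The gain may be small.** Baseline pain and disability plausibly overlap with the baseline PSFS, itself a function score, so the low end of the R² range is as credible as the high end. This stands. The case rests on asymmetry: about 1 power point lost at worst, against several gained if the covariates matter.

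**No false-positive problem.** A reader might infer from the words data-driven selection that false positives rise. The simulation shows a Type I error at or below nominal, within Monte Carlo error.

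**Power.** A reader might add that the trial already falls short of its stated power. An unadjusted two-sided comparison with 66 per group does have only about 69%. But the plan always adjusts for the baseline outcome, and at r = 0.5 the SE of 1.06 gives about 81%. Whether 66 completers suffice depends on r (65 needed at 0.5, 72 at 0.4, 78 at 0.3), which the document does not give. The point does not need this claim.

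**The wording clash.** It does not affect the primary PSFS model if disability means another measure. For the secondary pain and disability outcomes it needs tidying, no more.

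**Conclusion.** The point holds as an inefficient and weakly justified rule that should be fixed. It is not a threat to validity: no bias or inflation of false positives is shown.

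The covariate subset depends on chance imbalance, changing in about 23% of trials at an assumed p<0.05 trigger. Against always adjusting for the five listed covariates, the cost ranges from none (fixed adjustment is about 1 power point worse if they explain nothing) through about 3 points at 10% of residual variance to about 10 points at 30%. Reported standard errors under the rule are about 1–5% too large at p<0.05.

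These sizes rest on the assumed correlation of 0.5, independent candidates, the assumed R² range and trigger, and a one-time-point analysis in place of the mixed model. The direction of the argument, that imbalance is the wrong criterion for adjustment, needs none of them.

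**What to change.** Remove the condition from the covariate sentence and fix one set for every model, whatever the observed balance: the outcome's own baseline value plus the covariates the protocol already lists. Condition (LBP or knee OA) may be added; it was not part of the simulation, so no gain is claimed for it. Where a listed baseline is also the outcome's own baseline, as for the pain and disability outcomes, enter it once. In the same edit, say which measure disability refers to, because the Secondary outcomes section uses different questionnaires for the two conditions. Keep the baseline table as description only, with no role in choosing covariates.

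The cost is a few degrees of freedom out of about 130, and about 1 power point if the covariates prove not to be prognostic. The wording can be settled in the promised SAP. Because the rule stands in the protocol, the change also needs a small amendment, which the Protocol amendments section routes through the ethics committee. It should be made before any comparison of the groups at baseline is used for modelling.

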### Outcome measures

Outcome measures will be taken through an online link via REDCap at baseline, at 3 and 6 months follow-up post-randomisation.

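### The protocol names the group-by-time interaction as the treatment effect in a baseline-adjusted mixed model, but that term is not the adjusted between-group difference

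*Protocol article*

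**What the plan says.** Three places in the protocol article bear on this.

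- **Statistical analysis.** The effect of group allocation on continuous outcomes "will be assessed through group*time interaction terms using linear mixed models with baseline value as covariate". The sentence covers the primary outcome (the Patient-Specific Functional Scale, PSFS) and the continuous secondary outcomes. It does not say which time points form the outcome rows, and it names no between-group contrast at month 3 or month 6. The same section adds: "The focus of the analyses will be on effect estimation rather than formal hypothesis testing".
- **Outcome measures.** Data are collected "at baseline, at 3 and 6 months follow-up post-randomisation", so there are two visits after baseline.
- **Sample size.** "Sample size calculation was based on the between-group difference of 3 points on our primary outcome". The quantity of interest there is a difference between groups, not a change in that difference over time.

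The Statistical analysis section also promises a public statistical analysis plan before analysis. That plan is not at hand.

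**The concern.** The sentence fixes two things at once: which term carries the treatment effect, and that baseline enters as a covariate. The two do not fit together well.

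Once baseline is a covariate, the natural outcome rows are months 3 and 6. The interaction then describes how the effect changes between those visits, not how large it is. If baseline is kept as an outcome row as well, the interaction does measure the treatment effect, but as a plain difference in change, and the stated baseline adjustment hardly touches it.

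What is at stake is the headline estimate. For the same data with a sustained 3-point benefit, one reading reports about 0 and the other about 3. A plan that puts effect estimation first should not leave that open.

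**Working it through.** **Inputs from the protocol article.** Visits at baseline, 3 and 6 months (Outcome measures). Target difference 3 points, SD 7, 78 per group (Sample size).

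**Assumption, not in the documents.** The correlation rho between visits, taken as 0.3, 0.5 and 0.7, equal for all pairs of visits.

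The plan gives no figure for the interaction term, so there is none to reproduce. The 3 points and SD of 7 only set the scale.

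**Reading A: months 3 and 6 are outcome rows, baseline is a covariate.** Write g = 1 for eHealth and 0 for usual care:

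E[Y] = a + b·baseline + c·(month 6) + d·g + e·g·(month 6)

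- Effect at month 3 = d. Effect at month 6 = d + e.
- Interaction e = effect at month 6 − effect at month 3.
- Sustained benefit (3, 3): e = 3 − 3 = 0.
- Fading benefit (3, 1.5): e = 1.5 − 3 = −1.5, although eHealth is better at both visits.

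This is algebra and needs no value of rho.

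**Reading B: baseline, month 3 and month 6 are all outcome rows, and baseline is also a covariate.** Each row of a participant contains the same b·baseline. In the within-person difference (month 6 − baseline) it cancels. The month-6 interaction is therefore the between-group difference in mean change. It is unbiased under randomisation, but it gains nothing from b.

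Variances with n per group:

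- Difference in change: 2·SD²·(1 − rho)·(2/n)
- Adjusted contrast at one visit: SD²·(1 − rho²)·(2/n)
- Ratio: 2(1 − rho)/(1 − rho²) = 2/(1 + rho)

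With SD 7 and n = 78:

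| Assumed rho | SE, difference in change | SE, adjusted contrast | Variance ratio |
|---|---|---|---|
| 0.3 | 7·√(1.4·2/78) = 1.33 | 7·√(0.91·2/78) = 1.07 | 2/1.3 = 1.54 |
| 0.5 | 7·√(1.0·2/78) = 1.12 | 7·√(0.75·2/78) = 0.97 | 2/1.5 = 1.33 |
| 0.7 | 7·√(0.6·2/78) = 0.87 | 7·√(0.51·2/78) = 0.80 | 2/1.7 = 1.18 |

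The ratio does not depend on n or on the SD.

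**Simulation check.** 150 trials, 78 per group, complete data, SD 7, rho 0.5, true effect 3 points at both visits, random-intercept mixed models:

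- Reading A, group contrast at month 3: mean 3.02, average SE 0.97.
- Reading A, interaction: mean 0.01, average SE 1.11.
- Reading B, month-6 interaction with the baseline covariate: mean 3.06, average SE 1.115.
- The same model without the covariate: mean 3.06, average SE 1.115. The two estimates never differed by more than 3 × 10⁻¹³.

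Both sets of results agree with the algebra.

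**The case against.** The strongest reply is that there is a third reading. The same model, with months 3 and 6 as outcomes and baseline as covariate, yields the right quantity if the group-by-visit terms are coded as visit-specific differences or combined into such contrasts afterwards. The text speaks of the effect of group allocation and uses the plural for the terms, and the trial is sized on a between-group difference. All of this suggests that the authors want the difference at each visit. Row structure, coding and contrasts are also things that an analysis plan commonly settles.

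Much of this stands. A reader might infer that the model itself is wrong, and the documents do not support that. The plural does not decide the matter, because the sentence covers several outcomes. The promised analysis plan does not remove the point either: the protocol does not leave the term open but names it, and as named it is the wrong term or a less precise one.

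Three other stronger inferences also fail.

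- *That the second reading is biased.* It is not. A difference in change answers the stated aim of improving function compared with usual care. The cost is precision, and that cost shrinks as rho rises.
- *That the trial would wrongly conclude there is no effect.* This needs the single reference-coded coefficient from Reading A to be reported alone, and the section puts estimation ahead of testing.
- *That baseline adjustment would restore the stated power.* The sample size section uses a plain comparison of two means and claims no gain from baseline. At rho 0.5 the variance of a change score, 2·SD²·(1 − 0.5), equals SD², so Reading B is then as precise as the comparison on which the trial was sized. Whether that sample size is adequate is a separate matter.

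Finally, the statement that the covariate adds exactly nothing holds for complete data with a random intercept. The plan allows for 15% loss at six months and says "No attempt will be made to impute missing values", so small differences could appear in practice.

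**Conclusion.** The point holds as a fault in the named term, not in the model class. With only the follow-up visits as outcomes, the standard interaction coefficient has expectation 0 for a sustained 3-point benefit and −1.5 for one that fades to 1.5 points; this rests on algebra alone. With baseline also an outcome row, the estimate is unbiased, but its variance is 1.54, 1.33 or 1.18 times that of the adjusted contrast at rho 0.3, 0.5 or 0.7. Those ratios rest on an assumed correlation, equal between all visits and with the same SD at each, for which the documents give no value. On either of these two readings the named term is not the baseline-adjusted between-group difference. It should be corrected before analysis, because the sentence governs the primary outcome and the readings can give very different headline estimates from the same data. Nothing here bears on the stated sample size or power.

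**What to change.** Replace the sentence with a model and an explicit estimand, in the protocol by amendment or in the analysis plan:

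- Model PSFS at months 3 and 6 on group, categorical time, group-by-time and baseline PSFS, with repeated measures within participant. Keep baseline out of the outcome rows.
- Define the treatment effect as the adjusted between-group difference at each visit: the group effect at month 3, and the group effect plus the interaction at month 6. In Stata this is lincom or margins after mixed.
- Report the interaction only as the change in effect between months 3 and 6.

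An equally acceptable alternative is a constrained longitudinal analysis: baseline, month 3 and month 6 as outcomes, a common baseline mean in both groups, and no baseline covariate.

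The same wording should apply to the continuous secondary outcomes. The cost is one or two sentences and one post-estimation command, with no extra data or participants.

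### The condition subgroups (LBP, knee OA) are planned as separate analyses with no group-by-condition interaction named; one pooled model would estimate the difference directly at almost no cost

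*Protocol article*

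**What the plan says.** The Aim section sets one pooled question, for "people living in rural Australia with chronic non-specific LBP or knee OA". It states no aim of comparing the effect between the two conditions.

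The Statistical analysis section says that treatment effects on continuous outcomes "will be assessed through group*time interaction terms using linear mixed models with baseline value as covariate". On subgroups it has one sentence: "A subgroup analysis stratified by condition (LBP or OA) will be performed separately". No group-by-condition term is named anywhere in the article.

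Two other sentences in that section bear on the point: "The focus of the analyses will be on effect estimation rather than formal hypothesis testing", and "A statistical analysis plan will be made publicly available before analysis". That analysis plan is not available here.

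The primary outcome, the PSFS, is the same scale in both conditions. Only the activity-limitation outcome uses different instruments (RDQ for low back pain, WOMAC for knee osteoarthritis).

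**The concern.** Two within-condition results answer two separate questions: what the effect is in back pain, and what it is in knee osteoarthritis. Neither is an estimate of the difference between them, and neither carries a standard error for that difference. The group-by-condition contrast supplies both.

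Condition is the only subgroup factor the article names, and the trial combines two diagnoses with different age limits under one primary estimate. Readers will ask whether the pooled result applies to both. If all they have is two results, each on about half the sample, they may conclude that the intervention works in one condition and not in the other when the data do not show this.

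**Working it through.** **Inputs.** From the Sample size section: "Sample size calculation was based on the between-group difference of 3 points on our primary outcome"; "the response within each subject group on physical function was normally distributed with a standard deviation of 7"; 78 per group; 15% loss. Evaluable per arm: 78 × 0.85 = 66.3, taken as 66. The split between conditions is not given, so 50:50 is an assumption, and 70:30 and 80:20 are shown beside it. Tests below are two-sided at 5%.

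**The plan's own figure.** Two-sided, n = 2 × (1.960 + 0.842)² × 7² / 3² = 86 per group, or 86 / 0.85 = 102 after loss. One-sided at 5%, n = 2 × (1.645 + 0.842)² × 7² / 3² = 68, or 80 after dividing by 0.85 (79 after multiplying by 1.15). The stated 78 is close only to the one-sided result, and the article does not state sidedness. What follows uses only the difference, the SD and the numbers evaluable, so it does not depend on this.

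**Reading by significance.** Let the true effect be 3 points in both conditions, with p1 and p2 the t-test power in each. The chance that exactly one is significant is p1(1 − p2) + p2(1 − p1).

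| Split | Evaluable per arm, by condition | p1 | p2 | Exactly one significant |
|---|---|---|---|---|
| 50:50 | 33 and 33 | 0.403 | 0.403 | 2 × 0.403 × 0.597 = 0.48 |
| 70:30 | 46 and 20 | 0.529 | 0.262 | 0.51 |
| 80:20 | 53 and 13 | 0.589 | 0.183 | 0.56 |

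A simulation of 40,000 trials at 33 and 33 gave 47.8%. Baseline adjustment does not remove the problem: with an assumed baseline correlation of 0.5 (SD × √0.75), the three figures are 50%, 55% and 62%. With no effect in either condition, the chance is 2 × 0.05 × 0.95 = 9.5%.

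**Reading by estimates.** The SE of the difference between the two condition-specific effects is 7 × √(2/n1 + 2/n2), where n1 and n2 are the numbers per arm in each condition. The chance that two estimates of the same true effect lie 3 points or more apart is 2 × (1 − Φ(3/SE)).

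| Split | SE of interaction | Apart by 3 points or more |
|---|---|---|
| 50:50 | 7 × √(4/33) = 2.44 | 22% |
| 70:30 | 7 × √(2/46 + 2/20) = 2.65 | 26% |
| 80:20 | 7 × √(2/53 + 2/13) = 3.06 | 33% |

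The main-effect SE is 7 × √(2/66) = 1.22.

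**What an interaction test does.** With the same true effect in both conditions, it signals a difference in 5% of trials (4.9% in the simulation). Its power for a true 3-point difference between conditions at 50:50 is Φ(3/2.44 − 1.96) + Φ(−3/2.44 − 1.96), about 23%. Across splits from 50:50 to 80:20, 66 or 78 per arm, and baseline correlation 0 or 0.5, that power runs from 17% to 34%.

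**The case against.** The best reply is that the article does not commit to what is criticised. It nowhere rules out a group-by-condition term, it promises an analysis plan, and the terms of a subgroup model normally belong there. The word *separately* may mean only apart from the main analysis. All of this stands: the point can be put no more strongly than that no such term is named. Even so, stratifying by condition most naturally describes within-condition fits, and the wording can be improved whatever the analysis plan says.

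Second, a reader might infer that the trial will report a false difference about half the time. The documents do not support that. The figure near 50% needs a real effect and a comparison of the two p-values, whereas the article puts estimation ahead of testing and plans no comparison between conditions. The fairer figure for an estimation reading is 22% at an even split. Estimation is also a reason to report the contrast and its interval.

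Third, the two sets of participants are independent, so a careful reader can obtain the difference and an approximate interval from the two estimates. That is true, and it makes this a matter of model and reporting, not an invalid analysis.

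Fourth, it is tempting to say that the pooled diseases are measured on different scales. That applies only to RDQ and WOMAC, whose raw scores cannot share a model; separate analysis is natural there.

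Finally, the interaction is weakly powered. This stands too: a wide interval would not show that the effects are equal.

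**Conclusion.** The point holds in a limited form. The article plans condition-specific analyses and names no group-by-condition interaction, so as written it gives no direct estimate or test of whether the effect differs between conditions. If both conditions share a true effect of 3 points, with SD 7 and 66 evaluable per arm, exactly one would be significant 48% to 56% of the time over splits from 50:50 to 80:20. The two estimates would lie 3 points or more apart 22% to 33% of the time. The split is an assumption throughout, and these ranges take no credit for baseline adjustment.

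The documents do not show that an interaction has been excluded or that a claim of a difference is intended. Severity is minor: a free improvement that can be made in the analysis plan before analysis.

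**What to change.** For the outcomes common to both conditions (PSFS, pain intensity, quality of life, physical activity, pain self-efficacy), obtain the condition-specific effects from one pooled mixed model. It should contain group × condition and group × condition × time, with their lower-order terms.

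Report the interaction estimate and its 95% CI beside the two condition-specific differences, and state that any claim of a difference between conditions rests on that estimate. Label it exploratory and state its precision: SE about 2.44 points at an even split and 2.65 at 70:30, against 1.22 for the main effect. It is twice the main-effect SE only when the split is even.

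Keep RDQ and WOMAC analysed separately by condition.

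The cost is a sentence or two in the analysis plan and a few extra model terms, with no new data and no change in sample size.
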